## Abstract

**Background:**

For the monitoring of International Normalized Ratio (INR) values, venous thromboembolism (VTE) and atrial fibrillation (AF) patients can visit anticoagulation clinics, laboratories, or physicians for venous puncture. Point-of-care testing (POCT) made it possible for patients to monitor INR themselves (self-monitoring) and even self-adjust their medication dosage (self-dosage). Both skills are accepted as forms of self-management. eHealth applications can improve this self-management, resulting in better clinical outcomes.

**Methods:**

Our study, called PORTALS, aims at identifying the optimal implementation strategy of training to improve self-management and explore factors that enhance good self-management skills. In addition, the relationship between the implementation strategy of training, clinical outcomes, and individual characteristics will be investigated. Of the 247 recruited participants, 110 chose to continue with regular care. 137 patients have been randomly divided in subgroups and compared using a parallel cohort design: one group will be trained and educated by e-learning, and the other group will receive face-to-face group training.

**Discussion:**

More insight in factors that enhance good self-management will help to improve clinical outcomes and patient satisfaction on anticoagulation therapy. Our study will provide practical insights and knowledge of eHealth in daily practice and of the importance of education on the adoption of self-management. We expect the self-management program including training to help patients to better manage their own INR values and medication use, thereby increasing health status and diminishing thromboembolic events and hospitalisation.

**Trial registration:**

The Netherlands National Trial Register, number NTR3947.

## Background

Venous thromboembolism (VTE) and atrial fibrillation (AF) are common causes of mortality and morbidity, and are associated with high medical costs [1]. With the ageing population and persisting unhealthy lifestyles, the prevalence of VTE and AF is rising rapidly [2]. Treatment of VTE and AF patients consists of, among other interventions, anticoagulant therapy (AT) with vitamin K-antagonists to treat, slow down, or prevent formation of blood clots [2]. AT demands frequent monitoring of blood samples to measure its effects. Results are expressed as International Normalized Ratio or INR values. In 2009 there were over 385.000 patients in the Netherlands who were treated with anticoagulants, more than half of whom suffered from AF (211.000 patients) [3]. Between 2005 and 2009 the number of VTE patients in the Netherlands increased by 13%; the prevalence of AF patients increases every year, especially amongst males due to the rising survival rate of myocardial infarcts [4].

For the monitoring of INR, patients have to visit anticoagulation clinics, laboratories, or physicians for venous puncture. This is one of the major disadvantages of anticoagulant therapy with vitamin K antagonists and, together with frequently occurring unstable anticoagulation, one of the reasons that other anticoagulants (novel oral anticoagulants, NOACs) are being developed and often preferred as an alternative [5]. However, since the alternatives show disadvantages and risks too, improving procedures around vitamin K antagonists attract attention [6].

Point-of-care testing (POCT) is one of these potential improvements: it generates rapid test results and has been widely implemented in the last decade. POCT made it possible for patients to monitor INR values themselves (self-monitoring) and, as a next step, to even self-adjust their medication dosage (self-dosage). The major benefit of this self-management approach is the increased involvement of patients in their own care process, thus resulting in improved adherence to AT, and thereby reduction of complications. Research showed that self-management in AT patients decreases the risk of thromboembolic complications and mortality at a constant frequency of bleeding complications [7]. Several published studies and systematic reviews have suggested methods of monitoring anticoagulation therapy may be equal to or better than standard monitoring by a physician. Patients who self-monitor or self-dose can improve the quality of their oral anticoagulation therapy [8]. When patients start with self-monitoring or self-dosage, they receive structured education and training in self-testing and adjustment of medication dosage. In addition, eHealth applications are developed in the form of online web portals to share self-measured INR values with care professionals. These web portals also provide programs that support self-adjustment of medication dosage. Research showed that self-management with online support results in improved INR values (Time in Therapeutic Range, TTR, of 10–23%) compared to self-management without online support (less than 4% improvement of TTR) [9, 10]. Moreover, patient satisfaction is higher when using online remote monitoring of INR [11]. Based on these results we conclude that eHealth applications do improve self-management of vitamin K antagonist anticoagulant therapy, resulting in better clinical outcomes.

In the last few decades, self-management has become an important strategy for coping with chronic illnesses. Adequate self-management requires the individual ability to deal with symptoms, treatment, and physical and social consequences of a disease. The basic principle of self-management is that behavioral change cannot succeed without patients taking their responsibility [12]. Research on other chronic diseases such as diabetes [13], COPD [14], and heart failure [15] showed that personality aspects such as self-efficacy are important factors in successful self-management. This notion is derived from the social cognitive theory, which states that behavioral change is made possible by a personal sense of control. Self-efficacy has been described as the “belief in one’s capabilities to organize and execute the course of action required to produce given attainments”.

As education is the basic approach in development of self-management skills, we expect that the strategy to implement the educational support largely affects the individual level of self-management and thereby clinical outcomes. However, it is clear that self-management is not a ‘one-size-fits-all’ intervention. How can self-management skills then be optimized in a large groups of individuals, such as patients with AT? Which factors positively influence the acceptance of self-management? To answer these questions for patients with AT we designed the PORTALS study.

Our goal is to analyze the effect of the implementation of e-learning versus a group training on top of a program of self-monitoring or self-management. In addition we will investigate the relationship between the implementation strategy of training, clinical outcomes, and individual patient characteristics.

We consider both self-monitoring and self-adjustment of medication as important self-management skills. In this study we defined self-management skills as the usage of the self-management platform; the amount of login sessions. For this definition, the difference between self-monitoring and self-dosage is not relevant. Self-monitoring and self-dosage activities are registered within the same login session. Therefore, we make no distinction between patient-self-dosage and patient-self-testing in this study. All skills are accepted as forms of self-management.

## Methods

In this study, self-management will be offered to patients of the Saltro Thrombosis Service (outpatient anticoagulation clinic and laboratory), who currently receive usual care for long-term AT.

Usual care consists of frequent monitoring of blood samples to measure the effects of vitamin K-antagonists. These blood samples are taken by classical venipuncture at primary care locations or at home. Based on the INR, specialized medical doctors define the acquired dosage for individual patients and follow puncture; patients receive the advice and instruction on individual basis.

We used a parallel cohort design to investigate determinants of optimal implementation; we will compare the different training methods. After inclusion, participants will be randomly divided in subgroups: one group will be trained and educated by e-learning (group 1) and the other group will receive face to face group training (group 2). Both the e-learning and the group training consist of at least three components: i) disease-specific knowledge of VTE; ii) self-testing skills; iii) use of the web portal; and iv) self-adjustment of medication. The fourth module is voluntary. Hence, 2 groups of self-management patients will be formed. Patients who do not wish to start with self-management will be invited to participate in the non-self-management group, a parallel cohort group describing usual care (group 3). They continue to receive regular care of high quality. In Fig. 1 the inclusion of the research groups is summarized.

**Fig. 1 Fig1:**
[figure not shown]
Subdivision within the Saltro Thrombosis Service into three groups; Groups 1 and 2 perform self-management; group 1 was instructed by e-learning and group 2 by group course. Group 3 receives the usual care, with brief instructions

Due to the nature of this study (implementation research in a real-life care setting) a perfect RCT design is not feasible: patients cannot be forced to start self-management. Patients will however be randomized in group 1 (e-learning) and group 2 (group training). Furthermore, patients unable to dose their medication are free to continue with only self-monitoring. This study will be performed using a parallel cohort design. Although bias may occur, the results of this study remain valuable because in daily practice biases will occur too when it comes to patients voluntary choosing the type of care they are willing to receive. Based on our study design, comparison between e-learning and group training for self-management (group 1 and 2) and non-self-management patients (group 3) is applicable considering specific conditions in the choice of the statistics. Parallel cohort group 3 provides valuable information about patients who are unable or unwilling to use online supported self-management programs.

### Power calculation

In thrombosis patients clotting speed is expressed in INR values. Optimal INR values vary between individual norms. Therapeutic effects are expressed as the percentage of Time the patient is in the Therapeutic INR Range (TTR). A pilot study of 100 patients of the Saltro Thrombosis Service Centre shows that the average TTR is 84% (SD 10). Research shows that TTR improves significantly in self-management compared with usual care, with 5–13% increasing TTR [16]. To prove a relevant effect of the new implementation strategy of e-learning or group training (>5%) at a power 80% and α = 0.05, 63 patients must be included per group. Taking into account a 15% drop out, 72 (63/0.85) patients are needed per study group.

Previous studies reported a 21–77% response at inclusion of study [8, 9, 17]. Even if attrition rate at inclusion would be only 21%, there are sufficient eligible patients to reach an adequate sample size: at 21% attrition rate, 343 patients (72/0.21) must be approached per group to include sufficient participants in the study. As this study includes three research groups, a total of at least 1029 patients is needed to complete the study. Currently, 8950 patients receive usual care from the Saltro Thrombosis Service.

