### Intervention

This study investigates the effect of different implementation strategies on adequate training for self-management skills in patients with AT expressed in TTR, as well as potential determinants of the effect. We compare group training versus e-learning. Patients who follow e-learning have to pass at least three modules. The first module contains general education about anticoagulation including test questions. Patients can only successfully pass this first module after all questions are answered correctly. They then receive a written confirmation. With this confirmation patients can pick up a self-testing device at one of the Saltro Thrombosis Service locations. Furthermore, patients get access to the second module that teaches them to use the self-testing device. After one or two weeks patients have an appointment with a nurse of the Thrombosis Service Centre to show their self-testing skills. If the skills are sufficient, the nurse explains the patients how to use the online web portal. The following three months a training period is applicable, during which patients measure their INR weekly and inform the Thrombosis Service using the web portal. After three months, patients have another control appointment to check their self-testing skills technique and adequate use of the web portal. If patients are able to provide reliable INR values by self-measurement and if they adequately use the web portal to inform the Thrombosis Service about testing results and relevant medical information, the self-monitoring training is ended. From that moment on, patients have control appointments with the nurse every six months. In addition, patients are offered to continue with training in self-adjustment of medication dosage. This training is only available in a group course.

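### The 5-point planning effect is supported only by evidence on self-management versus usual care; for the randomised e-learning versus group-training contrast, the achieved numbers give 76% power at 5 points after the planned dropout

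*Protocol article*

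**What the plan says.** The Background of the protocol article gives the aim: "Our goal is to analyze the effect of the implementation of e-learning versus a group training", on top of a self-management programme that both arms follow. Only groups 1 and 2 are randomised; group 3 (usual care) is the patient's own choice (Allocation procedure).

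The Power calculation reports that in a local pilot of 100 patients "the average TTR is 84% (SD 10"). Its only effect evidence is "Research shows that TTR improves significantly in self-management compared with usual care, with 5–13% increasing TTR". The next sentence begins "To prove a relevant effect of the new implementation strategy of e-learning or group training (>5"%) and continues "at a power 80% and α = 0.05, 63 patients must be included per group". It does not say what e-learning or group training is compared with. Dropout follows: "Taking into account a 15% drop out, 72 (63/0.85) patients are needed per study group". Recruitment of patients reports 63 randomised to e-learning and 74 to group training.

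On the content of training, the Methods section says "Both the e-learning and the group training consist of at least three components" and lists self-adjustment of medication as the fourth, voluntary one. The Intervention section, describing the e-learning arm, says of self-adjustment training: "This training is only available in a group course". It says the same for the group-training arm.

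**The concern.** A planning effect should belong to the contrast that it sizes. The cited gain of 5 to 13 points is what patients obtained by self-managing instead of receiving usual care. In groups 1 and 2 everybody self-manages, with self-testing, the web portal, three months of weekly measurement, a check at three months and six-monthly nurse appointments. The arms differ in the delivery, order, timing and gating of the training. Evidence on the first contrast says nothing direct about the size of the second.

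The stated 80% power may therefore be taken as describing the randomised question when nothing in the section supports that. A non-significant result for group 1 versus group 2 could then be given more weight than the data can carry.

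The dosage module adds to this. If self-adjustment is taught only in a group course, e-learning patients who go on to it also receive group teaching. A conclusion about e-learning as a four-component method would then go beyond what was delivered by e-learning.

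**Working it through.** **Inputs.** Difference 5 points, SD 10, power 80%, α 0.05 and dropout 15% (Power calculation); 63 and 74 randomised (Recruitment of patients). Sidedness is not stated; two-sided is used because it reproduces the plan's figure (one-sided would give 50).

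**1. The plan's own figure.** n per group = 2 × (1.960 + 0.842)² × 10² / 5² = 62.8, so 63. This reproduces. A t-test calculation gives 63.8, so 64. Side note on dropout: 63/0.85 = 74.1, not 72, and group 1 was randomised at exactly 63, so it carries no dropout allowance.

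**2. Numbers for group 1 versus group 2.** After 15% dropout: 63 × 0.85 = 53.6 and 74 × 0.85 = 62.9, about 54 versus 63.

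**3. Standard error.** SE = 10 × √(1/n1 + 1/n2).
- No dropout: 10 × √(1/63 + 1/74) = 1.71.
- After dropout: 10 × √(1/53.6 + 1/62.9) = 1.86.

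**4. Detectable difference at 80% power.** By the normal approximation, (1.960 + 0.842) × SE.
- No dropout: 2.802 × 1.71 = 4.8 points (t-test 4.84).
- After dropout: 2.802 × 1.86 = 5.2 points (t-test 5.25).

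**5. Power, two-sided t-test, SD 10.** The documents give no expected e-learning versus group-training difference, so the rows below 5 points are assumptions.

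| True difference | 63 vs 74 | after 15% dropout |
|---|---|---|
| 5 | 83% | 76% |
| 4 | 64% | 57% |
| 3 | 41% | 36% |
| 2 | 21% | 19% |

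**6. Precision.** 95% CI half-width = t × SE. No dropout: 1.978 × 1.71 = 3.4 points. After dropout: 1.981 × 1.86 = 3.7 points.

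**7. The contrast that the evidence does concern.** For self-management versus usual care (137 versus 110, less 15% dropout), power for 5 points is about 95% by the normal approximation. The cited effect fits that contrast, which is not randomised.

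**8. The dosage module.** Methods lists self-adjustment within both the e-learning and the group training. Intervention offers it to both arms as a group course only. Both statements cannot describe the e-learning method.

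**The case against.** Four objections have weight.

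*The main comparison is not settled.* Outcome parameters and Data analyses put the three-group comparison first and group 1 versus group 2 second, and the Power calculation counts three groups. On that reading the cited evidence fits the contrast being sized. This stands to the extent that group 1 versus group 2 cannot be called the primary analysis. It remains the stated goal and the only randomised contrast, and the section still names no comparator.

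*Five points may be a minimum relevant difference.* The text speaks of a relevant effect above 5%. Sizing on a relevant difference is legitimate whatever the true effect, and 63 per group is then right. This also stands. Falling power below the design difference is no error in itself; the shortfall at 5 points comes from the achieved numbers and the planned dropout.

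*Dropout may not apply in full to TTR.* The service registers INR values itself (Data collection), so a patient lost to questionnaires need not be lost to TTR. For that reason both sets of figures are shown.

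*The dosage module is voluntary and offered alike to both arms.* True, but the two descriptions of the e-learning method still disagree.

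Stronger readings are tempting and are not supported:
- A reader might infer that a null result is likely. That needs a true difference below about 3.4 points (3.7 after dropout), and the documents give no figure.
- A reader might infer that a null result will be reported as no difference. The article does not say how it will be read, and its mixed models yield estimates and intervals.
- A reader might take the 377 of 1,271 existing self-management patients who self-dose and dilute the effect by that share. They are not the trial's participants, and nothing says that the arms' difference vanishes among self-dosers.

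**Conclusion.** The point holds in a limited form. The 5-point effect is backed only by evidence on self-management versus usual care, the 80% power is attached to no named contrast, and no reason is given for expecting 5 points between two ways of teaching self-management.

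The 63 per group is not an arithmetical error. The shortfall at 5 points is modest: 76% instead of 80% if the planned dropout occurs, and none if it does not. The larger uncertainty is whether differences smaller than 5 points matter or are to be expected. If they are, the randomised contrast has limited power.

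These figures assume SD 10 as in the pilot, a two-sided 5% test, an unadjusted comparison of two means, and dropout equal in both arms. The planned adjustment for age and gender and the mixed model could change them somewhat.

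**What to change.** In the Power calculation, state that the 5–13% evidence concerns self-management versus usual care. Then give power and detectable difference for group 1 versus group 2 at the achieved numbers: 76% for 5 points and about 5.25 points after 15% dropout, or 83% and 4.8 points without dropout. If 5 points is meant as a minimum relevant difference for that contrast, say so and give the reason.

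Add one sentence that a non-significant group 1 versus group 2 result will be read from its estimate and 95% CI (half-width about 3.7 points after dropout) and not as evidence of no difference. A similarity margin of ±5 points is not proposed: it equals the lower end of the cited self-management benefit, so a format that lost almost all of that benefit could be called alike.

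Reconcile the Methods and Intervention sections on how self-adjustment training is delivered, and limit the e-learning conclusion to the modules actually delivered by e-learning.

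The cost is wording and a slightly less favourable power statement. No extra patients or data are needed.

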### Recruitment of patients

Patients of the Saltro Thrombosis Service who receive regular care will be recruited. In 2013, 8950 patients received usual care from the Saltro Thrombosis Service, of which 85% with long-term indications. A random selection of 1632 patients was approached for participation in the study using three methods:First a randomly selected group of 475 patients was informed by letter. Of these, 233 patient responded and 59 were willing to participate in the study.Second we approached patients through personal invitation by nurses of the Saltro Thrombosis Service who collect blood by venipuncture. All nurses were trained by the research team to inform patients well about the study and research goals. During five months, nurses actively informed 692 patients about self-management. Of those, 139 patients were interested to participate in the study. In addition, 234 were interested in self-management too, but not in participation in the study.Third we recruited patients by telephone. Two trained research assistants called patients at home to inform them about the possibilities of self-management and about the study. By telephone 465 patients were approached, of which 111 were willing to participate in the study. In addition, 52 patients signed up for self-management but were not willing to participate in the study.

Participants were only included in the study after written informed consent was received. Because not all patients signed an informed consent, 247 participants were finally included. Of these, 110 continued to receive regular care and 137 patients were randomly divided in group 1 and 2 using a computer program. In group 1 (e-learning) 63 patients were included and in group 2 (group training) 74 patients were included. In Fig. 2 recruitment is summarized.

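### The dropout inflation is miscalculated (63/0.85 gives 75, not 72), and with 63 patients in e-learning the randomised comparison has about 76% power, not 80%, at the planned 15% dropout

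*Protocol article*

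**What the plan says.** The Power calculation section takes a mean TTR of 84% with SD 10 from a pilot of 100 patients and sets a relevant effect of more than 5 percentage points. It concludes that "at a power 80% and α = 0.05, 63 patients must be included per group". For dropout it states: "Taking into account a 15% drop out, 72 (63/0.85) patients are needed per study group". It then uses the 72 to plan the approach: "at 21% attrition rate, 343 patients (72/0.21) must be approached per group", and multiplies by three groups to reach 1029.

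The Recruitment of patients section gives the final numbers. Of 247 included patients, 110 stayed in regular care and 137 were randomised: "In group 1 (e-learning) 63 patients were included and in group 2 (group training) 74 patients were included".

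No section, including the limitations in the Discussion, compares these numbers with the target or restates the power.

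**The concern.** Two things go wrong in sequence. The printed formula does not give the printed result, and the error runs in the unfavourable direction: the stated target is too small to leave 63 completers per group. The e-learning arm then closed at 63, the number needed before any dropout. It is 9 below the printed target and 12 below the corrected one.

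This affects e-learning versus group training, which is the only randomised comparison and the goal stated at the end of the Background. A reader of the Power calculation section would assume that this comparison keeps 80% power after 15% dropout. On the article's own inputs it does not. If the result is null, the power behind it will be quoted as higher than it was.

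**Working it through.** **Inputs**
- Difference 5 TTR points, SD 10, α 0.05, power 80%, dropout 15%, response 21% (Power calculation).
- Randomised: 63 in e-learning, 74 in group training; not randomised: 110 in regular care (Recruitment of patients).
- Sidedness is not stated. Two-sided is inferred because it returns 63; one-sided would give 50.

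**Step 1. Base sample size**

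n = 2(z₀.₉₇₅ + z₀.₈₀)² × SD² / difference² = 2 × (1.96 + 0.8416)² × 100 / 25 = 62.8, so 63 per group. The article's base figure reproduces with the normal approximation. The t-test version gives 63.8, so 64.

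**Step 2. Dropout inflation**

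- Formula as printed: 63 / 0.85 = 74.1, so 75.
- Check on the printed result: 72 × 0.85 = 61.2 completers, below 63.
- Check on the corrected result: 75 × 0.85 = 63.75 completers, which is enough.
- The printed 72 matches 63 × 1.15 = 72.45. That is a common shortcut and probably the source, but it is not the formula shown.

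**Step 3. Figures that depend on 72**

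- As printed: 72 / 0.21 = 342.9, so 343; 3 × 343 = 1029.
- Corrected: 75 / 0.21 = 357.1, so 358; 3 × 358 = 1074.

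**Step 4. Power of the achieved randomised sample**

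Completers at 15% dropout: 63 × 0.85 = 53.55 and 74 × 0.85 = 62.9.

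Standard error = 10 × √(1/53.55 + 1/62.9) = 1.859.

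Power = Φ(5/1.859 − 1.96) = Φ(0.729) = 76.7%. The t-test version gives 76.0%.

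Detectable difference at 80% power = (1.96 + 0.8416) × 1.859 = 5.21 points (5.25 by t-test).

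**Step 5. Where the loss comes from**

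| Scenario (difference 5, SD 10) | Evaluable per arm | Power, normal | Power, t-test |
|---|---|---|---|
| Plan before dropout | 63 / 63 | 80.1% | 79.5% |
| 72 per arm, 15% dropout | 61.2 / 61.2 | 79.0% | 78.3% |
| Achieved, no dropout | 63 / 74 | 83.1% | 82.5% |
| Achieved, 15% dropout | 53.55 / 62.9 | 76.7% | 76.0% |

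The division error alone takes power to 79.0%. The rest of the drop to 76.7% comes from the e-learning arm stopping at 63. With the achieved arms, power falls below 80% once dropout exceeds about 7% by the normal approximation, or about 6% by t-test. That is roughly half the planned rate.

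**The case against.** Neither the wrong quotient nor the size of the e-learning arm can be disputed. The case on the other side is that little follows from them.

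- **The slip is small and the approach figures no longer matter.** This is true. It costs about one point of power, and 1632 patients were approached, more than either 1029 or 1074. The printed numbers are still wrong and easy to correct.
- **Group training is not really short.** This stands. 74 × 0.85 = 62.9 completers against an unrounded requirement of 62.8. It misses 75 only through rounding. The shortfall lies in e-learning.
- **Part of the gap comes from the choice of test.** By t-test even 63 evaluable per arm gives 79.5%. On the article's own normal approximation the shortfall is 3.3 points (80 − 76.7), so it does not depend on changing method.
- **The powered comparison is not clearly named.** The effect is drawn from studies of self-management versus usual care, and the target is applied to three groups. At 15% dropout regular care keeps 110 × 0.85 = 93.5 patients, and power against it is 83.1% for e-learning and 86.6% for group training. This stands as a limit on scope: the shortfall concerns e-learning versus group training only. The comparisons with regular care are not randomised, and these percentages make no allowance for adjusting for confounding.
- **Dropout may be lower and the model may add precision.** INR values are recorded by the thrombosis service, so TTR need not be lost when a questionnaire is. The mixed model adjusts for age and gender. A variance reduction of about 8% would restore 80%, since 1 − (5/5.21)² = 0.08. This is plausible, but the article claims no such gain, and 15% is its own planning figure.
- **The article never claims 80% for the achieved sample.** Not in those words. It prints the target and the achieved numbers without comparing them, which leaves the planning figure as the only statement of power.

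**Conclusion.** The point holds. 63/0.85 is 74.1, so the target should read 75 per group, and the figures of 343 and 1029 are wrong in consequence. With 63 and 74 randomised and the planned 15% dropout, e-learning versus group training has 76 to 77% power for a 5-point TTR difference. The stated 80% applies to a difference of about 5.2 points (5.21 normal approximation, 5.25 t-test).

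The loss is modest: between 3 and 4 points of power, or about 0.2 TTR points in detectable difference. It comes mainly from the e-learning arm. The result assumes a two-sided test, SD 10, equal dropout of 15% in both arms and an unadjusted comparison of two means. It does not extend to the comparisons with regular care.

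**What to change.** In the Power calculation section, correct 72 to 75 per group, 343 to 358 approached per group, and 1029 to 1074 in total, and state that the test is two-sided.

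Then add one sentence, there or in Recruitment of patients, on the achieved sample. For example: with 63 and 74 patients randomised and 15% dropout, the comparison of e-learning with group training has about 76% power to detect a difference of 5 TTR points, and 80% power for a difference of about 5.25 points (two-sample t-test, SD 10). If the authors prefer the normal approximation used for the base figure, the pair is 76.7% and 5.21 points. Both numbers should come from the same method.

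The cost is a wording correction and a slightly less favourable power statement. Enrolment, allocation, outcomes and analyses do not change.
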